### Objectives

The purpose of the proposed research [acronym: AGECAR (Activity in GEriatric Acute CARe)] is to investigate the effect of an intrahospital multi-time per day physical training program, consisting of walking and strength training of the lower limbs, during a short period of hospitalization in seniors aged 75 years or older on functional capacity at discharge (primary outcome). The effect of the physical training program will be compared to a control group receiving normal hospital care. Besides length of hospitalization, the secondary outcomes that will also be assessed at hospital admission and discharge will be pulmonary ventilation (forced expiratory volume in one second, FEV_1_) and peripheral oxygen saturation. The secondary outcomes that will be assessed by telephone interview three months after discharge will be mortality, number of falls after discharge, and ability to cope with activities of daily living (ADLs, using the Katz ADL score and Barthel ADL index).

Increased age and a history of falls in the previous year are associated with decreased functional capacity [11], and handgrip strength is a predictor of survival [20] and mobility [21]. On the other hand, low cognitive ability, reflected as low scores on the Mini-Mental Status Examination (MMSE) is associated with increased chance of decreased functional capacity upon discharge [11,22]. Thus, we will also determine if age, history of falls in the previous year, handgrip strength and MMSE scores (covariates) will have an influence on the effects of the training program on the aforementioned primary and secondary outcomes. The major hypothesis is the prescribed training program will increase functional capacity at discharge while decreasing length of hospitalization.

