### Statistical analysis

To assess the training effects on the study outcomes, we will analyze the data according to the intention-to-treat principle [37]. When post-test data are missing, baseline scores will be considered post-test scores. We will use a two-factor (group and time) analysis of variance (ANOVA) with repeated measures. We will repeat the analysis using the actual blinding of assessment staff to participant randomisation assignment (successful or not), baseline values of age, body mass index, MMSE, number of falls within the previous year and handgrip strength as covariates. For each outcome variable we will report the level of significance corresponding to the main group (between-subjects), time (within-subjects) and interaction (group × time) effects. We will perform post hoc pre- vs. post comparisons by group only when a significant group*time effect is present. The level of significance will be set to = 0.05. We will adjust multiple comparisons for mass significance [38]. We will use the Student’s *t* test (or its non-parametric equivalent, the Mann Whitney’s *U* test) for comparing between the two groups the mean values of those secondary outcomes that will be assessed only once, i.e. three months after discharge (number of falls, Katz score and Barthel index). We will compare mortality rate at three months after discharge in the two groups with the chi square test.

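### With one admission and one discharge value, the planned group × time ANOVA is a valid change-score test but less precise than comparing discharge values adjusted for admission, and its main effects do not measure efficacy

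*Protocol article*

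**What the plan says.** The Objectives section of the protocol article sets the target as the effect of training, against normal hospital care, "on functional capacity at discharge (primary outcome"). SPPB and 10-metre walk time (primary) and FEV1 and SpO2 (secondary) are each assessed at admission and at discharge.

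For these outcomes the Statistical analysis section states: "We will use a two-factor (group and time) analysis of variance (ANOVA) with repeated measures". It continues that for each outcome "we will report the level of significance corresponding to the main group (between-subjects), time (within-subjects) and interaction" effects. Within-arm contrasts are conditional: "We will perform post hoc pre- vs. post comparisons by group only when a significant group*time effect is present". A general multiplicity statement follows: "We will adjust multiple comparisons for mass significance".

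The analysis is then repeated with blinding success and "baseline values of age, body mass index, MMSE, number of falls within the previous year and handgrip strength as covariates". The admission value of the outcome itself is not on that list. For missing discharge data the rule is: "When post-test data are missing, baseline scores will be considered post-test scores".

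Length of stay and the three-month outcomes have no admission–discharge pair and are outside this point.

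**The concern.** Three p-values are to be reported per outcome, but only one of them, the interaction, estimates what the trial set out to learn. The group main effect averages a pre-treatment value, where no effect can exist, with the discharge value. The time effect pools the arms. The follow-up contrasts, if reached, are before–after comparisons inside each arm. A reader of the results could take any of these as the treatment effect.

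The interaction itself uses the admission value inefficiently. It subtracts that value in full instead of giving it the weight that the data support. The covariate-adjusted repeat does not recover this, because it adjusts for other baseline characteristics and not for the admission score. What is at stake is precision that the trial has already paid for, and a clear single estimate of the effect.

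**Working it through.** **Inputs.** From the sample size section: 60 per group, significance level 0.05 (two-sided assumed), power above 80%, 20% loss, 150 in total. From the outcome sections: two occasions. Not in the article: the SD, the mean admission SPPB and the admission–discharge correlation ρ. ρ is therefore an assumption, shown from 0.3 to 0.9.

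**The plan's own figure.** The loss step reproduces: 120 / (1 − 0.20) = 150. The 60 per group cannot be re-derived without an SD. Solved backwards, it corresponds to a standardised difference of (1.960 + 0.842) / √(60/2) = 0.511.

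**Step 1: what the interaction tests.** With two occasions, the group × time F equals the square of the t statistic comparing change scores between arms. In a simulated data set of 60 per arm, both were 9.7664.

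**Step 2: precision.** Take equal SDs σ at both occasions and independent patients. The variance per patient is:

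- change score: 2σ²(1 − ρ)
- discharge adjusted for admission (ANCOVA): σ²(1 − ρ²) = σ²(1 − ρ)(1 + ρ)
- ratio, ANCOVA to change score: (1 + ρ)/2

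Suppose that 60 per arm gives exactly 80% power for the interaction. ANCOVA then needs 60 × (1 + ρ)/2 per arm for the same power. Kept at 60 per arm, it has the power in the last column.

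| ρ (assumed) | Variance ratio | ANCOVA n per arm for 80% | ANCOVA power at 60 per arm |
|---|---|---|---|
| 0.3 | 0.65 | 39 | 93.5% |
| 0.5 | 0.75 | 45 | 89.9% |
| 0.6 | 0.80 | 48 | 87.9% |
| 0.7 | 0.85 | 51 | 86.0% |
| 0.8 | 0.90 | 54 | 84.0% |
| 0.9 | 0.95 | 57 | 82.0% |

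Now hold the discharge difference at 0.511 SD with 60 per arm. Power for interaction against ANCOVA is 65.8% against 83.6% at ρ = 0.3, 80.0% against 89.9% at 0.5, and 95.1% against 97.5% at 0.7. Simulation with 4,000 runs each gave 80.3% against 90.0% at ρ = 0.5, and 94.4% against 97.0% at 0.7.

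**Step 3: the group main effect.** It compares the patient mean of the two occasions, so it targets half the discharge difference, with variance σ²(1 + ρ)/2. At ρ = 0.5 the standardised effect is (0.511/2)/√0.75 = 0.295, which gives 36.6% power at 60 per arm. Over ρ = 0.3 to 0.9 the power runs from 41% down to 30%. The time effect contains no comparison of arms.

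**Step 4: the carry-forward rule.** A patient whose admission score is reused has a correlation of 1 by construction. As an illustration, if 20% were carried forward (the maximum loss that the article assumes) and these patients were otherwise like the rest, ρ = 0.6 becomes 0.2 × 1 + 0.8 × 0.6 = 0.68 (ratio 0.84), and ρ = 0.7 becomes 0.2 × 1 + 0.8 × 0.7 = 0.76 (ratio 0.88). The rule thus moves the trial towards the lower rows of the table, where the gain is smaller.

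**The case against.** The strongest defence is that the interaction is a legitimate between-arm test and that nothing in the section is false. The sample size section also speaks of a clinically relevant change and of expected improvement in controls, so a test of differential change fits how the trial was sized. Both points stand. Under randomisation, though, change-score and adjusted analyses target the same difference, so the precision argument is untouched.

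Three stronger readings are tempting, and the article does not support them.

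- **Uncontrolled type I error.** A reader might infer this from three p-values plus within-arm tests. However, the within-arm tests are allowed only after a significant interaction, and a multiplicity adjustment is stated. The article assigns no separate error rate to the main effects. Which term is confirmatory may be set out in a fuller document, so its absence here is not the criticism.
- **A biased change score that ANCOVA would cure.** Allocation by four-week period makes baseline imbalance plausible, and a reader might conclude that adjustment removes it. That depends on how the imbalance behaves. Take a 0.2 SD imbalance and ρ = 0.6. If it regresses at the patient-level slope, the change score is off by (1 − 0.6) × 0.2 = 0.08 SD and ANCOVA by 0. If it is a case-mix shift that persists fully to discharge, the change score is off by 0 and ANCOVA by 0.08 SD. The article does not say which applies.
- **A fixed saving in patients.** Ratios of 0.75 to 0.85 hold for ρ of 0.5 to 0.7, which is assumed. Short stays, the same investigator for SPPB and walk tests, a familiarisation session and carried-forward scores could all favour a higher ρ. At 0.9 the saving is only 5% of variance.

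**Conclusion.** The point holds as one of efficiency and focus. For SPPB, 10-metre walk, FEV1 and SpO2, the one treatment-relevant term in the planned model is a change-score comparison. It is valid, but less precise than adjustment for the admission value at any ρ below 1. The ANCOVA variance is 65% to 95% of the change-score variance for ρ from 0.3 to 0.9, with the upper end made more likely by the carry-forward rule. These figures assume equal SDs at both occasions and independent patients. Neither model as described deals with clustering by four-week period, which is a separate matter. The group and time main effects do not estimate the discharge difference between arms and should not be read as evidence of efficacy. No inflation of type I error and no systematic bias is shown.

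**What to change.** Make the primary analysis of SPPB and 10-metre walk time, and likewise of FEV1 and SpO2, the between-arm difference in the discharge value adjusted for the admission value of the same measure. Report it as one estimate with its 95% CI. Keep the article's pre-specified covariates, including blinding success and body mass index, for the repeat analysis, alongside the admission value. If the group and time main-effect p-values or the within-arm before–after tests are still reported, label them descriptive and do not present them as evidence of efficacy.

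The cost is a change of wording in the analysis section. The admission values are already collected, and the recruitment target of 150 need not change. The change should not be justified as a protection against imbalance between four-week periods, because that depends on how such imbalance carries through to discharge.

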### Covariates

Besides actual blinding success of assessment staff to participant randomisation assignment, the following covariates will be measured in all participants upon hospital admission as they could influence one or more of the study outcomes.

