#### *History of falls within the previous year*

We will record the participants’ history of falls within the 12-month period prior to hospital admission. A fall will be defined as an “unexpected event in which the participants come to rest on the ground, floor, or other lower level” [33,34].

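### Three-month falls are compared without adjustment for the prior-year falls already collected, so the comparison gives up some precision at no saving in data

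*Protocol article*

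**What the plan says.** Under Statistical analysis, the protocol article first describes a two-factor (group and time) repeated-measures ANOVA. It then says this analysis will be repeated with blinding success and "baseline values of age, body mass index, MMSE, number of falls within the previous year and handgrip strength as covariates". Only after that does it turn to the outcomes with a single assessment. For these ("number of falls, Katz score and Barthel index") it names Student's t test or the Mann-Whitney test "for comparing between the two groups the mean values of those secondary outcomes that will be assessed only once, i.e. three months after discharge". No covariate is mentioned for these tests.

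Elsewhere the article shows that the relevant covariate exists and why it is collected:

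- History of falls within the previous year: "We will record the participants’ history of falls within the 12-month period prior to hospital admission".
- Covariates: "the following covariates will be measured in all participants upon hospital admission as they could influence one or more of the study outcomes".
- Objectives: "Thus, we will also determine if age, history of falls in the previous year, handgrip strength and MMSE scores (covariates) will have an influence"; this refers to training effects, for both the primary and the secondary outcomes.

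**The concern.** As written, physical performance at discharge will be adjusted for earlier falls, but falls themselves will not. A group-by-time model needs at least two occasions, so the adjusted repeat has no meaning for a count taken once at three months, and neither a t test nor a Mann-Whitney test accepts a covariate. The section therefore gives no route by which falls history could enter the falls comparison, although the Objectives extend the covariates to secondary outcomes.

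What is at stake is precision. If patients who fell before admission tend to fall again, part of the between-patient variation in three-month falls can be explained by information already in hand. An analysis that leaves it unexplained has a wider confidence interval and less power than the same patients could give.

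**Working it through.** **Inputs from the article.** Two groups of 60, significance level 0.05, power above 80%, 20% loss and 150 recruited (Sample size and statistical power). These are set for the SPPB; no power, fall rate or correlation is given for falls.

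**The plan's own figure.** 120 / (1 − 0.20) = 150, which agrees. The 60 per group cannot be rebuilt, because no standard deviation is given. At two-sided 0.05 (assumed; sidedness is not stated) and 80% power, 60 per group corresponds to a standardised difference of (1.96 + 0.84) × √(2/60) = 0.511.

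**Effect of adjustment.** Let r be the correlation between prior-year and three-month falls (an assumption, range 0.1 to 0.6). Linear adjustment multiplies the residual variance by 1 − r². For an effect with 80% unadjusted power:

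adjusted power = Φ(2.80 / √(1 − r²) − 1.96); equivalent n per arm = 60 × (1 − r²), rounded up.

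| r | Variance removed | Adjusted power | Equivalent n per arm |
|---|---|---|---|
| 0.1 | 1% | 80.4% | 60 |
| 0.2 | 4% | 81.6% | 58 |
| 0.3 | 9% | 83.6% | 55 |
| 0.4 | 16% | 86.4% | 51 |
| 0.5 | 25% | 89.9% | 45 |
| 0.6 | 36% | 93.8% | 39 |

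Example, r = 0.4: √0.84 = 0.917; 2.80 / 0.917 = 3.06; 3.06 − 1.96 = 1.10; Φ = 86.4%. The gain reaches 5 points at r of about 0.36.

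**Check with count data.** Falls are skewed counts, so the formula was checked by simulation: 60 per arm, 1,500 trials per setting, and Poisson counts with a gamma-distributed fall risk that each patient keeps from before admission to after discharge. Assumed means were 1.0 prior-year fall and 0.5 three-month falls, with a rate ratio of 0.5. The adjusted model was quasi-Poisson with log(prior falls + 0.5).

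| Observed r | t test | Mann-Whitney | Adjusted count model |
|---|---|---|---|
| about 0.22 | 54% | 48% | 55% |
| about 0.36 | 46% | 41% | 51% |
| about 0.52 | 38% | 32% | 50% |

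With no true effect, rejection rates for these three methods lay between 3.5% and 5.9%. Each power has a simulation standard error of at most √(0.25 / 1,500) = 1.3 points.

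**If fall risk does not persist fully.** Further runs used a three-month mean of 0.6, the same rate ratio, 2,000 trials and variances of the patient-level risk of 0.5, 1.0 and 1.5. The gain over the t test was about 1, 5 and 10 points with full persistence; 0, 2 and 4 with a correlation of 0.7 between underlying risk before and after the stay; and −1, 1 and 3 with a correlation of 0.5. In the runs without full persistence the observed counts correlated only 0.13 to 0.34. A separate recomputation gave about 2, 5 and 11 points with full persistence, 1 to 5 at 0.7 and −2 to 2 at 0.5.

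**The case against.** The strongest reply is that nothing here is invalid. An unadjusted two-group comparison of a secondary outcome is standard, it holds its error rate, and the trial was never sized for falls, so the 80% starting point is hypothetical. That stands, and it limits the point to efficiency.

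Nor is a large gain shown. Prior falls are recalled by older inpatients over 12 months, the later count covers three months, and an acute illness lies between. Prior falls are thus a prognostic covariate and not a true baseline measurement of the outcome. This also stands: with imperfect persistence the simulated gain is a few points or none.

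The sentence in the Objectives can be read as being about effect modification, which a main-effect covariate would not test. That is a fair reading. The sentence still shows that the covariates were meant to matter for secondary outcomes.

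The remaining reply is that a condensed article may leave adjusted secondary analyses to a fuller plan. This carries less weight, because the article does not leave the analysis open: it names the test, and that test cannot use the covariate. If the adjusted repeat was meant to cover the three-month outcomes, the text does not say so.

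A reader might infer three stronger claims that the document does not support:

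- **That the unadjusted test would take a chance excess of prior fallers in one arm for a training effect.** Chance imbalance is already allowed for in the test's error rate; it costs precision and does not bias the comparison on average.
- **That adjustment would answer the allocation by four-week periods.** It would not remove clustering by period, and the simulations contain no period effects.
- **That the chi-square test for mortality is equally deficient.** The article gives no death rate or strength of association from which a gain could be worked out. With possibly few deaths, an adjusted model is a debatable trade.

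**Conclusion.** The point holds as one of efficiency for a single secondary outcome. The section fixes an unadjusted test for three-month falls, and its adjusted analysis cannot apply to them, although prior-year falls are collected and the covariates are intended to bear on secondary outcomes.

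The size depends on a correlation that the article does not give: a gain of at most about 4 points of power at r of 0.3 or less, about 6 at 0.4 and about 10 at 0.5, from an assumed 80%. The larger gains require that fall risk before admission largely carries over to the months after discharge. The stated test remains valid in the sense checked here, with independent patients, and the primary conclusion is untouched.

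**What to change.** In Statistical analysis, take number of falls out of the t/Mann-Whitney sentence. State that three-month falls will be compared with an over-dispersed count model (negative binomial or quasi-Poisson) on group, adjusted for number of falls in the year before admission; age may be added. Fix the form of the prior-falls term in advance; log(prior falls + 0.5) is one workable choice. Keep the unadjusted test as a supportive analysis, and leave the mortality test as it is.

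The cost is wording only, since the covariate is already recorded at admission. There are two small downsides: the effect is reported as a rate ratio and no longer as a difference in means, and the gain may be only a few points if earlier falls predict later ones weakly. Clustering by four-week period needs its own remedy.

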## Discussion

The increase in life expectancy has resulted in a large segment of the population in industrialized countries being over 75 years of age. As the population ages the number of individuals over 75 years of age who are hospitalized and are not able to live independently, will likely increase. This increase in the older segment of the population and the number of older individuals hospitalized calls attention to health care systems and public health policymakers to focus on promoting methods to improve functional capacity of this sector of the population. The present study examines the feasibility and effect of an intra-hospital physical training program during brief hospital stays. Results from the current study will help to better understand the potential of this type of physical training for improving the well being of older individuals.

## Abbreviations

ADLs: activities of daily living; ANOVA: analysis of variance; BMI: body mass index; FEV1: forced expiratory volume in one second; MMSE: Mini-Mental State Examination; QOL: quality of life; RCT: randomised controlled trial; SaO2: peripheral oxygen saturation; SPPB: Short Physical Performance Battery.
